## Discussion

Severe traumatic musculoskeletal injuries in children are treated in the emergency department by a specific treatment strategy, but for most common non-traumatic musculoskeletal complaints no standardized and evidence based treatment strategy exists. To our knowledge, this is the first randomized controlled trial investigating the effect of MT on children complaining of back and neck pain. This is important due to the potential long-term consequences of musculoskeletal complaints in children and the lack of evidence based treatments. It is necessary to focus research efforts on how to best treat and prevent these complaints at an early age.

Many adults experience complaints in more than one region of the spine and therefore it is increasingly common to investigate the effect of manipulative therapy on complaints involving the whole spine rather than region-specific complaints [36, 37]. Symptoms from the various regions are very similar [38, 39], and pain in different regions of the spine may be closely interrelated. Furthermore, new research have shown that in children pain is likely to progress to more locations [13]. Therefore it is an important aspect of this study that the spine is treated both as one entity and as three separate regions.

The strengths of this study are that it is school based and nested in a large longitudinal cohort study where the children were monitored every week for two and a half years, and the pragmatic design makes the interventions easy to implement in daily practice. During the study period both groups received optimal pragmatic usual care with MT as the only difference. Therefore any difference in the results obtained between the two groups can be attributed to MT alone. For ethical reasons, we did not have a control group receiving no treatment, and we did not compare with “real life” usual care, which often is probably less than our pragmatic usual care. Because of the pragmatic setup, we did not have standardization on number or duration of treatment. However, in the analyses, we will determine if the number of visits differed between groups and if that is the case, the number of visits will be included in the explanatory models.

Blinding of the children and the practitioners was not possible due to the nature of the treatment. The results might be influenced by the interaction between the children and the practitioners; that includes verbal communication, physical contact and empathy between the two parts. These non-specific factors cannot be measured and we do not know the full influence of them in this trial. All children were however treated by more than one clinician, which will enhance generalizability, and choice of treatment in the individual consultation depended on the treating chiropractor.

A limitation of the study is, that we did not systematically ask for side effects to the treatment; it was only recorded if told by the child or if the practitioner occasionally asked for it. A systematic recording of side effects should be implemented in future studies

If it is possible to develop efficient treatment for back and neck pain in children and adolescents, a life course of recurring problems may be altered with potential positive implications for both individuals and society. And because it is very rare to have serious side effects to manipulative therapy in children, potentially just mild side effects as soreness or reddening [40], the possible implications in terms of improved spinal health and wellbeing may be considerable.

Furthermore, fast and complete recovery from back and neck pain will minimize the restrictive impact of the pain on the level of physical activity and thus potentially have a positive influence on general health. This is exceedingly important in this age group where the level of physical activity tend to decrease [41–43], which might have a significant impact on future health [44, 45], and where lifetime habits are being developed [43, 46].

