### Interventions

#### The non-manipulative group received

Pragmatic advice such as the use of cold or hot packs, braces, taping, suitable activities, ergonomics etc.Exercises including self-stretching and/or strengthening exercisesSoft tissue treatment in the form of manual trigger point therapy and/or massage. Assisted stretching was not allowed in this group, as this would approach mobilization

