#### The manipulative group received

The items mentioned aboveManipulative therapy: joint manipulation consisting of high-velocity, low-amplitude manipulation and/or joint mobilization without a high-velocity impulse to the spine and/or the extremities where indicated based on movement restriction and/or pain response during movement palpation

Thus, manipulative therapy was administered when there was a perceived biomechanical dysfunction of one or more joints that the treating clinician related to the child’s symptoms. The purpose of MT is to eliminate or relieve the pain as well as to reestablish better mobility and enhance the biomechanics of the joint, thus creating a basis for normalization of muscle activity around the joint [33–35].

In both groups, the frequency and content of treatments was determined on a pragmatic basis by the treating chiropractor. The treatment was intended to resemble pragmatic daily clinical practice in order to make the results more generalizable and implementable. The treatment continued until cessation of symptoms as determined by the child or parent or until the treating chiropractor decided that no further treatment was warranted. After 2 weeks of treatment, or earlier if the treatment was terminated, the child was questioned about global perceived effect, NRS and satisfaction with treatment. If there was no improvement in symptoms after 4–6 weeks of treatment, the child was referred to a secondary care spine center for a second opinion and further diagnostic work-up and/or imaging. The child and/or parents could stop the treatment at any time and still participate in other parts of the CHAMPS study.

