### Blinding

The interventions used in this trial make blinding of care providers impossible. The children were somewhat blinded because they were not told which group they were allocated to and the two groups would more or less have the same amount of treatment in terms of number of visits and time spent per visit. However, concealment of treatment group was difficult and some children might have detected the difference between the groups by comparing with their friends or by talking to their parents; or some may have had manipulative therapy before.

The parents filled in the weekly SMS-track at home independent of clinicians or researchers. For the analyses, the coding of treatment groups will be unknown to the primary investigator ([name]) and the statisticians performing the analyses, and the primary investigator is not involved in the treatments. The code will not be broken until the analyses are completed.

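### The Discussion credits any between-group difference to manipulative therapy alone, but the design supports only an effect of allocation to care that includes it

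*Protocol article*

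**What the plan says.** The Discussion of the protocol article states that "both groups received optimal pragmatic usual care with MT as the only difference" and draws from this that "any difference in the results obtained between the two groups can be attributed to MT alone". Neither statement is qualified.

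Other parts of the article describe the care and the blinding:

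- Interventions, manipulative group: "In both groups, the frequency and content of treatments was determined on a pragmatic basis by the treating chiropractor". Treatment ended when the child or parent judged that symptoms had gone, or when the chiropractor saw no need for more.
- Blinding: "The interventions used in this trial make blinding of care providers impossible". The children are described as partly blinded, with the warning that some may have worked out their group.
- Discussion, two sentences after the attribution claim: "we did not have standardization on number or duration of treatment". If the number of visits turns out to differ between groups, it is to be added to the models.
- Discussion, next paragraph: blinding of the children is now said to have been unachievable. Talk, touch and empathy between child and practitioner are named as possible influences, and "These non-specific factors cannot be measured and we do not know the full influence of them in this trial".

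**The concern.** Attribution to MT alone requires that everything else was the same in the two groups, or differed only by chance. Randomization secures this for characteristics present at entry. It does not secure it for care given afterwards by practitioners who know the allocation and may vary that care. If the manipulative group received different soft-tissue work, more contact or more encouragement, the effect of that would be part of the estimated difference.

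What is at stake is what the trial may conclude. A favourable result reported under this sentence would be read as a specific effect of manipulation. The Background stresses that MT is widely used in children without evidence, so the distinction matters to readers. The outcomes are not equally exposed. The two-week ratings of perceived effect and pain, given by the child, are the most exposed. The primary outcome comes from weekly parent text messages answered at home by parents who were not told the group, and is less so.

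**Working it through.** The attribution claim rests on no figure in the article, so there is none to reproduce. The check sets the claim against the rest of the text, then illustrates what a non-specific effect could do.

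**Step 1. Could anything other than MT differ between the groups?**

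- Co-treatment: yes. Frequency and content were at the chiropractor's discretion (Interventions), the chiropractor was not blinded (Blinding), and the Discussion repeats that the choice of treatment at each consultation lay with the practitioner. No rule holds soft-tissue work, exercises or advice equal.
- Contact: yes. Visits and time per visit are only expected to be about the same (Blinding). The Discussion says they were not standardized and plans for a difference in visits.
- Expectation and attention: yes. The article accepts that some children may have detected their group and that non-specific influences were not measured.

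**Step 2. Do the planned safeguards restore the claim?**

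- Not disclosing the group, home text-message replies and masked analysts reduce reporting and analysis bias. They do not equalize the care delivered.
- Expectation of treatment is a covariate, but it is asked before treatment starts. It cannot capture expectation formed by the treatment received.
- Number of visits is measured after randomization. Since treatment went on until symptoms ceased, a child who recovers faster has fewer visits, so visit number may itself reflect the treatment effect. Conditioning on it changes the quantity estimated and can introduce bias; it does not isolate MT.

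**Step 3. Illustration of size.**

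Inputs from the article: power of 76% for the primary outcome (Power considerations) and a 5% significance level (Statistical analyses). Assumptions: a two-sided test, a normal approximation for the log rate ratio, and a rate ratio behind the 76% of 0.75 to 0.85. That range is needed because the simulated scenario removed 20% of episodes and also halved the length of half of the episodes lasting two or more weeks, so it is not a pure 0.80 ratio. The non-specific ratios are assumed too.

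SE = |ln(ratio)| / (1.960 + 0.706). For 0.80: 0.2231 / 2.666 = 0.0837.

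With no specific MT effect and a non-specific ratio b, let d = |ln b| / SE. Then P(significant) = Φ(d − 1.96) + Φ(−d − 1.96). For b = 0.90 and SE = 0.0837: d = 0.1054 / 0.0837 = 1.26, giving 24.2%.

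| Ratio assumed behind 76% power | SE | b = 0.95 | b = 0.90 | b = 0.85 |
|---|---|---|---|---|
| 0.75 | 0.108 | 7.6% | 16.4% | 32.5% |
| 0.80 | 0.084 | 9.4% | 24.2% | 49.3% |
| 0.85 | 0.061 | 13.4% | 40.9% | 76.0% |

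Time at risk counts unaffected weeks, so both removing and shortening episodes should lengthen it. The ratio behind the 76% is therefore more likely below 0.80 than above, which points to the lower figures.

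**The case against.** The best defence is that this is one sentence in a Discussion. The stated objective is already the effectiveness of MT when added to other care, the analysis reports an incidence rate ratio for the intervention, and no analysis rule depends on the sentence. The article also discloses the lack of standardization and the non-specific factors close to the claim. This stands in part: the sentence is a claimed strength, and a reader who took it for a planned decision rule would go too far. But the caveats do not withdraw the claim. They sit beside it and contradict it.

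Three stronger readings are tempting and are not supported.

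- A reader might infer that the groups did differ in co-treatment or contact. The article permits this but shows no data that it happened.
- A reader might infer from "Assisted stretching was not allowed in this group, as this would approach mobilization" that the manipulative group received stretching as an additional co-treatment. The article does not list it for that group. The ban is there to keep care close to mobilization, which belongs to the article's definition of MT, out of the comparison group. It arguably protects the contrast.
- A reader might treat conditional delivery ("manipulative therapy was administered when there was a perceived biomechanical dysfunction of one or more joints") as a further contradiction. Children in the manipulative group who receive no MT dilute the contrast; they supply no rival cause of a difference. It does bear on wording, since the comparison concerns care that includes MT where indicated.

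It is also fair to say that the calculation shows only how bias inflates false positives, which is true of any trial. It does not estimate the bias in this one.

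**Conclusion.** The claim is wrong as written. An unqualified attribution to MT alone cannot stand beside discretionary care by unblinded practitioners, unstandardized contact, and the admission that non-specific influences were not measured. The safeguards limit the problem only in part.

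The randomized comparison itself is sound for the effect of allocation to care that includes MT where indicated. That fits the stated objective and the pragmatic aim, so no change of design or outcome is called for.

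The size cannot be determined from the documents. The range of about 16% to 41% for a 10% non-specific reduction rests on an assumed ratio of 0.75 to 0.85 behind the stated power, a two-sided test and a normal approximation. It is an illustration, not a finding about this trial.

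**What to change.** - Delete the statement that MT was the only difference. Replace the attribution sentence with one saying that the comparison estimates the effect of allocation to care that includes manipulative therapy where indicated, with any accompanying differences in co-treatment, contact and expectation, and that it does not isolate the specific effect of manipulation.
- Keep the analysis without adjustment for visits as primary, whether or not visits differ, and label the visit-adjusted model exploratory.
- Report the number of visits by group and, where the clinical register allows, the treatments received by group. The article does not show that each type of treatment is coded separately there, so the second part may not be possible.
- Reconcile the Blinding section, which calls the children partly blinded, with the Discussion, which says blinding them could not be done.

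The cost is wording, one label on an analysis and a descriptive table. The downside is a less favourable claimed strength.

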**Fig. 2 Fig2:**
[figure not shown]
Flowchart RCT

At baseline, the children filled in the KIDDS screen questionnaire that is a quality of life measure specifically designed for children [32] and answered a question about their expectations to the course of their treatment. In addition, they underwent an objective clinical examination including relevant neurologic and orthopedic examination as well as general and segmental movement palpation of the spine. General movement palpation is defined by the practitioner moving the spine in all directions and noticing the potential lack of movement, e.g. diminished forward bending of the neck. They then received a working diagnosis and were treated according to the randomization group. If the children did not fulfill the inclusion criteria, they were advised to remain active, and if necessary they were referred to examination and/or treatment elsewhere. If a child enrolled in the study experienced a recurrence of the original complaint or a new complaint during the remaining project period, the whole procedure was repeated starting with the phone interview and judgment of severity as defined previously. The only exception was randomization, as the child stayed in the original randomization group throughout the whole study period regardless of the number of recurrences or new complaints (incl. complaints in the extremities).

All clinical information was filed in a web-based register (Clinic Care Web), the KIDDS screen questionnaire, was paper-based and entered manually into Epidata, and data from the SMS were automatically stored in a secure database. Back up of all data were stored on a secure server at the University of Southern Denmark.

Data was monitored by an employed data manager throughout the project period.

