#### Secondary outcome measures

The average complaint time for each episode (measured in weeks).Information on pain site was collected from interviews and examinations and subsequently from the SMS-track. The number of recurrences and complaint time was collected by using data from the SMS-track (Additional file 1: appendix 1).Total duration of complaint time (measured in weeks). This was extracted from the SMS data (continuous variables).Global perceived effect after two weeks. The child was asked: how will you describe your general wellbeing now in your neck/back (and any extremities) as opposed to 2 weeks ago before treatment was started? This was rated on a 7-point Likert scale with 1 being much better and 7 being much worse.Change in pain intensity after two weeks. This was rated on an 11-point numerical rating scale where 0 is no pain and 10 is worst pain (continuous variable).

Finally, any side effects to the treatment were recorded at each clinical visit, if reported by the child.

In addition the following information was collected at baseline for descriptive purposes:Quality of life (KIDDS screen) (At baseline and at recurrent or new episodes).Expectations to treatment. The child was asked prior to treatment: how do you expect the course of your problem will be? This was rated on a 5-point scale with 1 being much worse and 5 being much better.Expectations to future course: if your problem goes away, do you expect it to recur? Answer: yes/no. (At baseline and at recurrent or new episodes).

Age (9–15 year), gender (boy, girl), educational level (1 = No qualification, 2 = Vocational training, 3 = Higher education < 3 years, 4 = Higher education 3–4 years, 5 = Higher education >4 years), intervention group (A, B), school (11 schools), grade (4^th^ to 9^th^ grade), physical education at school (extra physical education, normal physical education).

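### The Discussion's rule to add number of visits to the models when the arms differ conditions on a result of treatment and outcome, and nothing confines it to exploratory analysis

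*Protocol article*

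**What the plan says.** The rule is in the Discussion of the protocol article. After conceding that "we did not have standardization on number or duration of treatment", the authors write that they will check whether the arms differ in number of visits and, "if that is the case, the number of visits will be included in the explanatory models". The term explanatory models is not defined. No test or threshold is given for deciding that visits differ.

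Four other places show what the number of visits is:

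- **Interventions:** in both arms "the frequency and content of treatments was determined on a pragmatic basis by the treating chiropractor". "The treatment continued until cessation of symptoms as determined by the child or parent", or until the chiropractor judged that no more was warranted.
- **Procedure:** when an enrolled child has a recurrence or a new complaint, "the whole procedure was repeated starting with the phone interview and judgment of severity as defined previously". Only the randomisation step is skipped.
- **Participants and setting:** the phone interviewer may judge a complaint negligible, in which case the child is not seen.
- **Blinding:** care providers could not be blinded, and the arms were expected to have roughly equal numbers of visits.

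Statistical analyses gives the primary model as a hierarchical negative binomial regression of recurrences, with time at risk as exposure and school and class as random effects. Its covariate list for all analyses does not contain visits.

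**The concern.** Randomisation protects a comparison that conditions only on what was fixed before allocation. Number of visits is not fixed then. It can respond to the assigned arm, because an unblinded clinician chooses it and MT may change how soon symptoms stop. It can respond to the child's underlying severity, which also drives recurrences. It can also respond to recurrences themselves, which are the primary outcome.

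Holding visits constant compares MT children with control children who reached the same count for different reasons. If MT shortens care, an MT child with a given count tends to be a more severe case than a control child with that count, and the IRR is pushed upwards. If MT lengthens care, it is pushed downwards.

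The trigger compounds this. The covariate enters only when the arms are found to differ, and one way for them to differ is that MT works and fewer visits are needed. Without a defined criterion, the reported model also depends on the data.

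**Working it through.** The plan gives no figure for visits, so there is none to reproduce. Its 76% power for the primary outcome came from resampling the trial's own SMS data. The mean recurrence count and the dispersion are not stated, so that figure can be neither confirmed nor refuted, and it is not in dispute here.

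**From the protocol:** 237 children, 1:1 allocation, 3–27 months of follow-up, effect expressed as an IRR, 5% significance level, and a power scenario that removes 20% of episodes (taken here as a true IRR of 0.80).

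**Assumed, because the protocol is silent:** visit counts, mean recurrences, the severity effect, and the share of recurrences that lead to care.

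**Check 1: shared severity, no feedback from recurrences.** U is standard normal and T is 1 for MT.

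- visits ~ Poisson(4 · exp(gU) · f^T)
- recurrences ~ Poisson(4 · exp(gU) · R^T)

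Here R is the true IRR and f the visit ratio. A Poisson log-linear model was fitted to 200,000 simulated children, with and without visits.

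| g | True IRR | MT visits | IRR with visits in model |
|---|---|---|---|
| 0.4 | 1.00 | 15% fewer | 1.07 |
| 0.4 | 1.00 | 25% fewer | 1.12 |
| 0.4 | 1.00 | 15% more | 0.94 |
| 0.4 | 1.00 | 30% more | 0.89 |
| 0.4 | 0.80 | 25% fewer | 0.89 |
| 0.4 | 0.80 | 15% more | 0.75 |
| 0.2 | 1.00 | 25% fewer | about 1.04 |
| 0 | 1.00 | 25% fewer | 1.00 |

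Without visits the model returned the true IRR to within simulation error. In the fifth row, ln 0.89 / ln 0.80 = −0.117 / −0.223 = 0.52, so about half the log effect is lost. Using log visits instead of visits changes little.

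**Check 2: recurrences also generate visits.** Severity is as in check 1 with g = 0.4. Half of recurrences are assumed to lead to care, at 3 visits per treated episode including the first.

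| True IRR | MT visits per episode | IRR with visits in model |
|---|---|---|
| 1.00 | 20% fewer | about 1.15 |
| 1.00 | 25% more | 0.86 |
| 0.80 | unchanged | 0.88 |
| 0.80 | 20% fewer | 1.01 |
| 0.80 | 15% more | 0.80 |

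The third row shows attenuation when MT changes only recurrences. In the last row the two sources of bias happen to cancel.

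**Check 3: trial size, with the rule applied as a test-then-adjust procedure.** 237 children, follow-up uniform over 3–27 months, and negative binomial recurrences (mean 3–5, dispersion 0.25–0.5). Visits were generated by the first episode plus half of recurrences, at 3 per episode. Visits were compared by rank-sum test at 5%, and log visits was added if the test was significant. There were 300 runs per scenario, and school and class effects were omitted.

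- True IRR 1.00, MT changing only visits per episode (about 20% fewer or 27% more): the visit-adjusted IRR is 1.16–1.21 or 0.82–0.86. The rule rejects the true null in 28–39% of runs.
- True IRR 0.80, visits per episode equal: the visit-adjusted IRR is 0.87–0.90. Rejection is 0.32–0.52 under the rule, against 0.40–0.68 without visits.
- True IRR 0.80, fewer MT visits per episode: the visit-adjusted IRR is 1.02–1.07.
- True IRR 0.80, more MT visits per episode: the visit-adjusted IRR is 0.72–0.75.
- No effect on recurrences or visits: the visit-adjusted IRR stays near 1.00.

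Without visits, the IRR was 0.99–1.01 for a truth of 1.00 and 0.79–0.81 for a truth of 0.80. False positives were 3–8%, consistent with 5% over 300 runs.

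**The case against.** The best defence is that the sentence sits in the Discussion and speaks of explanatory models, a term that Statistical analyses does not use. If it means supplementary models beside an unadjusted primary result, the primary test is untouched and only interpretation suffers. That reading is open, so a reader who infers that the primary analysis will certainly be adjusted for visits goes further than the text. But the article does not state the supplementary reading either, and nothing reserves the main result for the model without visits.

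The Blinding section expects similar visit numbers, so the rule may never be triggered. That is an expectation only, and the rule exists for the case where it fails.

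Four further inferences are tempting and not supported:

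- **Every recurrence produces visits.** It does not. A counted recurrence needs only a positive SMS for the same region after a pain-free week, and the phone screen may end the matter there.
- **The article credits a visit-adjusted difference to MT.** The sentence "Therefore any difference in the results obtained between the two groups can be attributed to MT alone" comes before the visits rule and rests on the arms receiving the same care apart from MT. It makes no claim about an adjusted model.
- **Quality of life and expectations carry the same flaw.** Some are noted as collected "At baseline and at recurrent or new episodes", but the article presents them as baseline information and nothing says later values will be used as covariates.
- **Visits generated by recurrences always enlarge the bias.** With a true IRR of 0.80 and 15% more MT visits, the adjusted IRR is 0.75 without that feedback and about 0.80 with it.

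**Conclusion.** The concern holds in this form: the visits rule is wrong as written. Followed in any model used to report the treatment effect, it replaces the effect of being randomised to MT with a quantity that depends on how visits arose. The structural fault follows from the protocol's own account of how visits were determined and needs no simulation.

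Size and direction do depend on assumptions. With a severity effect of 0.4 per SD and 25% fewer MT visits, 1.00 becomes about 1.12 and 0.80 about 0.89. With a severity effect of 0.2, 1.00 becomes about 1.04. With no shared severity and no feedback from recurrences there is no bias. The 28–39% false-positive rate applies only if the rule governs the primary model and MT changes visits per episode by the amounts assumed. If the explanatory models are purely supplementary, the harm is to interpretation, and the Discussion and Statistical analyses still need to be reconciled.

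**What to change.** Replace the visits rule in the Discussion, and match it in Statistical analyses, with wording to this effect: all primary and secondary treatment effects are estimated without number of visits as a covariate; visits are reported descriptively by arm as part of the treatment received; any visit-adjusted or mediation model is labelled exploratory, with its assumptions stated. Interpret the main result as the effect of adding MT to pragmatic care, including any difference in visits that results.

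The cost is a sentence or two. No further data are needed, and no other part of the planned models changes. The change should be made before the treatment code is broken.
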